### Statistical Methods

2.7

*INCEPT‐Thromboprophylaxis* will use Bayesian statistical methods [36] with neutral, weakly informative priors, adaptive stopping and response‐adaptive randomisation, and probabilistic interpretation of results [28].

#### Analysis Sets and Primary Estimands

2.7.1

Analyses will primarily be conducted in the intention‐to‐treat population, with secondary analyses conducted in the per‐protocol population. The primary estimands in *INCEPT‐Thromboprophylaxis* are the sample‐average pairwise mean differences in the days alive out of hospital at 30 days between low, intermediate and weight‐adjusted dose LMWH in acutely admitted adult ICU patients with an indication for thromboprophylaxis with LMWH according to treatment allocation regardless of protocol adherence, with non‐survivors assigned 0 days.

#### Adaptive Analyses and Adaptations

2.7.2

Adaptive analyses will be conducted after completion of follow‐up and data collection/validation for the primary outcome for the first 1500 participants and every 500 additional participants until a maximum sample size of 10,000 participants. Constant, symmetrical stopping rules for superiority/inferiority of 99.5% and 0.5% are used; these stopping rules have been calibrated using simulations to ensure a type 1 error rate (the probability of erroneously declaring one arm overall superior) below 5% for the primary outcome. The domain will be stopped for practical equivalence if there is > 90% probability that the mean difference in the primary outcome is < 1 day [35, 37]. Stopping rules are binding [38]. Response‐adaptive randomisation based on each arm's probability of being superior will be used after the first adaptive analysis, with a minimum allocation of 25% to each arm (rescaled to 37.5% if one arm is dropped) [28, 35, 36].

#### Descriptive Statistics

2.7.3

Baseline data (Table 4), separation data and outcome data (Table 2) will be presented for each arm using medians with interquartile ranges for numeric data and counts with percentages for categorical data.

**TABLE 4 aas70199-tbl-0004:** Baseline data.

Characteristic	Fixed low dose LMWH (*N* = #)	Fixed intermediate dose LMWH (*N* = #)	Weight‐adjusted dose LMWH (*N* = #)
Country of enrolment			
Denmark	*n* (#.#%)	*n* (#.#%)	*n* (#.#%)
*[Each participating country listed separately in the domain report(s)]*	*n* (#.#%)	*n* (#.#%)	*n* (#.#%)
Age, median (IQR), years	## (## to ##)	## (## to ##)	## (## to ##)
Sex			
Female	*n* (#.#%)	*n* (#.#%)	*n* (#.#%)
Male	*n* (#.#%)	*n* (#.#%)	*n* (#.#%)
Weight, median (IQR), kg	## (## to ##)	## (## to ##)	## (## to ##)
Height, median (IQR), m	## (## to ##)	## (## to ##)	## (## to ##)
Use of invasive mechanical ventilation	*n* (#.#%)	*n* (#.#%)	*n* (#.#%)
Use of vasopressors/inotropes	*n* (#.#%)	*n* (#.#%)	*n* (#.#%)
Use of renal replacement therapy	*n* (#.#%)	*n* (#.#%)	*n* (#.#%)
Presence of a central venous catheter	*n* (#.#%)	*n* (#.#%)	*n* (#.#%)
Limitations of care	*n* (#.#%)	*n* (#.#%)	*n* (#.#%)
Co‐existing conditions			
Active haematological malignancy or metastatic cancer	*n* (#.#%)	*n* (#.#%)	*n* (#.#%)
History of ischaemic heart disease or heart failure	*n* (#.#%)	*n* (#.#%)	*n* (#.#%)
Diabetes mellitus	*n* (#.#%)	*n* (#.#%)	*n* (#.#%)
Chronic pulmonary disease	*n* (#.#%)	*n* (#.#%)	*n* (#.#%)
Chronic liver disease	*n* (#.#%)	*n* (#.#%)	*n* (#.#%)
Known use of immunosuppressive therapy within the last 3 months	*n* (#.#%)	*n* (#.#%)	*n* (#.#%)
Previous organ transplantation	*n* (#.#%)	*n* (#.#%)	*n* (#.#%)
Chronic dialysis	*n* (#.#%)	*n* (#.#%)	*n* (#.#%)
Treatment with antipsychotics at hospital admission	*n* (#.#%)	*n* (#.#%)	*n* (#.#%)
History of VTE	*n* (#.#%)	*n* (#.#%)	*n* (#.#%)
Suspected sepsis at ICU admission	*n* (#.#%)	*n* (#.#%)	*n* (#.#%)
Acute surgery within 7 days prior to randomisation	*n* (#.#%)	*n* (#.#%)	*n* (#.#%)
SMS‐ICU,^a^ median (IQR)	## (## to ##)	## (## to ##)	## (## to ##)
Predicted 90‐day mortality,^a^ median (IQR), %	##% (## to ##)	##% (## to ##)	##% (## to ##)
Predicted in‐hospital VTE risk,^b^ median (IQR), %	##% (## to ##)	##% (## to ##)	##% (## to ##)
Clinical Frailty Scale,^c^ median (IQR)	## (## to ##)	## (## to ##)	## (## to ##)
Lowest systolic blood pressure in the 24 h preceding randomisation, median (IQR), mmHg	## (## to ##)	## (## to ##)	## (## to ##)
Highest plasma lactate in the 24 h prior to randomisation, median (IQR), mmol/L	## (## to ##)	## (## to ##)	## (## to ##)
Highest plasma creatinine in the 24 h prior to randomisation, median (IQR), μmol/L	## (## to ##)	## (## to ##)	## (## to ##)
Lowest platelet count in the 24 h prior to randomisation, median (IQR), 10^9^/L	## (## to ##)	## (## to ##)	## (## to ##)

*Note:* Mock table illustrating how we plan to present baseline data. Binary or categorical variables are presented as numbers with percentages; numerical variables are presented as medians with interquartile ranges. Definitions of all baseline variables are provided in the core protocol [28] and full domain‐specific appendix [29].

Abbreviations: IQR, interquartile range; mmHg, millimetres of mercury; mmol/L, millimoles per litre; *N* or *n*, total counts or counts; SMS‐ICU, *Simplified Mortality Score for the Intensive Care Unit* [39]; μmol/L, micromoles per litre; VTE, venous thromboembolism.

^a^
SMS‐ICU [28] is a severity score (range 0–42 points) and prediction model, with higher values indicating more severe illness and higher risks of 90‐day mortality.

^b^
The predicted in‐hospital VTE incidence will be calculated using a modified version of the PROVE‐IT score [29].

^c^
Assessed by investigators using the Clinical Frailty Scale v2.0 [40] ranging from 1 (very fit) to 9 (terminally ill).

#### Primary Analyses

2.7.4

All outcomes will be analysed using Bayesian linear and logistic regression models adjusted for the stratification variables (site and history of VTE) and the following additional baseline variables: age (modelled using a linear and a quadratic term), sex, haematologic malignancy or metastatic cancer, acute surgery within 7 days prior to randomisation, invasive mechanical ventilation, circulatory support, renal replacement therapy within 72 h prior to randomisation, and time period (with a new period defined after each adaptation) [28]. Analyses will primarily use neutral, weakly informative priors not favouring any intervention, with sensitivity analyses using neutral, more informative (sceptical) priors and neutral, less informative priors, as well as evidence‐based priors for outcomes with relevant external evidence [29]. Results will be presented as sample‐average estimates and intervention effects on the absolute and relative scales with the absolute summary measures being the primary [28], all calculated using G‐computation with the posterior probability distributions [29]. Point estimates, 95% credible intervals, and probabilities of each intervention being overall superior as well as probabilities of superiority in each comparison, and—for the primary outcome—probabilities of practical equivalence between all arms, and probabilities of practical equivalence and differences larger than the equivalence threshold in both directions for each comparison, will be reported as outlined in the core protocol [28]. Model fitting and model diagnostics are described in the full core protocol [28, 29].

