#### Statistical Simulation and Performance Metrics

2.7.7

The *INCEPT‐Thromboprophylaxis* domain design has been developed and evaluated using statistical simulation via R v4.5.0 (R Core Team, R Foundation for Statistical Computing, Vienna, Austria) with the *adaptr* R package (https://inceptdk.github.io/adaptr) following the approach previously described and used [35, 37, 43]. The final design as well as sensitivity analyses with different design choices and key assumptions were all evaluated using 100,000 simulations under multiple clinical scenarios. In brief, we assumed that the distribution of the primary and guiding outcome in the different doses of LMWH arms resembled the distribution from the *AFIB‐ICU* cohort study [44]. This reference distribution was modelled using a *binomial* distribution handling the probability of having 0 or > 0 days, and a *beta* distribution modelling the distribution among those with > 0 days. In summary, 43.6% had 0 days (22.3% due to death), with an estimated mean of 18 days in those with > 0 days, and an overall estimated mean of 10 days. Simulations were conducted in scenarios with no differences between arms, and with no, small and large differences in both directions between arms, corresponding to overall mean differences of 1 or 2 days in either direction. Performance metrics were assessed under a total of 15 realistic scenarios, constituting all unique combinations of the reference distribution in one arm and no/small/large differences in the other arms in both directions. Multiple performance metrics were evaluated, with the key metrics presented in Table 6. The expected sample sizes across scenarios ranged from 2265 to 4892 participants, with approximately 100% probabilities of conclusiveness across scenarios.

**TABLE 6 aas70199-tbl-0006:** Key performance metrics of the final domain design.

Metric	No differences	Ranges across scenarios with differences
Sample size—mean	4867	2265–4892
[25; 50; 75%‐percentiles]	[3950; 4450; 5450]	[1950–3450; 1950–4950; 2450–5950]
Mean number of days alive out of hospital at 30 days—mean	10.3 days	9.0–11.9 days
[25; 50; 75%‐percentiles]	[10.2; 10.3; 10.4]	[8.9–11.8; 9.0–11.9; 9.2–12.1]
Probability of conclusiveness	~100.0%	~100.0% to ~100.0%
Probability of superiority	0.9%	4.0%–99.9%
Probability of practical equivalence	99.1%	0.1%–96.0%
Probability of inconclusiveness	~0.0%	~0.0% to ~0.0%
Probability of erroneous superiority	0.1%	~0.0% to 4.6%

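### The model for the primary outcome leaves out frailty and limitations of care, which the trial already records; adding them is a cheap, optional gain in precision of unknown but probably modest size.

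*Protocol article*

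**What the plan says.** Section 2.7.4 of the protocol article states that the regression models are "adjusted for the stratification variables (site and history of VTE) and the following additional baseline variables". The list then names "age (modelled using a linear and a quadratic term), sex, haematologic malignancy or metastatic cancer, acute surgery within 7 days prior to randomisation" and "invasive mechanical ventilation, circulatory support, renal replacement therapy within 72 h prior to randomisation", and ends with time period. It applies to all outcomes, through linear and logistic models, and cites the platform's core protocol.

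The mock baseline table in section 2.7.3 (Table 4) has a row for "Limitations of care" and one for frailty, with a footnote: "Assessed by investigators using the Clinical Frailty Scale v2.0". It also lists "Highest plasma lactate in the 24 h prior to randomisation" and "Lowest systolic blood pressure in the 24 h preceding randomisation", and body weight. None of these is in the primary model.

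The primary estimands (2.7.1) are sample-average mean differences in days alive out of hospital at 30 days. Section 2.7.7 describes the simulations through the marginal outcome distribution only: "43.6% had 0 days (22.3% due to death), with an estimated mean of 18 days in those with" more than 0 days. It mentions no covariate adjustment.

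**The concern.** The outcome combines survival and time in hospital. Frailty before the illness and a decision to limit treatment could each be expected to predict both. In the current set, age and cancer are at best partial stand-ins.

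In a linear model for a mean difference, adding prognostic baseline terms leaves the estimand unchanged and normally narrows the credible interval. This matters somewhat more here because section 2.5 replaces stratified allocation with simple response-adaptive randomisation after the first adaptive analysis. From then on, chance imbalance in prognostic factors is handled only by the model.

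At stake is efficiency: slightly wider intervals, and on average somewhat later stopping, than the data already being collected would allow.

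**Working it through.** **Inputs from the article.** Analyses at 1500 and then every 500 up to 10,000; stopping at 99.5%/0.5%; equivalence at more than 90% probability of a difference below 1 day; minimum allocation 25%, or 37.5% with two arms (2.7.2). 43.6% have zero days; the mean is 18 days among the rest and 10.3 overall (2.7.7, Table 6).

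**Inputs assumed.**
- *Standard deviation of the outcome* (not stated). Formula: variance = 0.564 × (s² + m²) − (0.564 × m)², where m and s are the mean and SD among those with more than 0 days. With m = 18.26 (which gives 10.3 overall) and s = 7: 0.564 × (49 + 333.4) − 106.1 ≈ 109.6, so SD ≈ 10.5. With m from 18 to 18.26 and s from 6 to 9, the overall SD is 10.0–11.3.
- *Lag.* 450 participants, inferred from the Table 6 percentiles (analysis at 3500, 3950 randomised).
- *Extra residual variance explained, R².* Given nowhere in the documents; 2–10% is taken as the working range.

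**Step 1: reproduce the stated design without covariates.** A three-arm simulation with these rules, normal posteriors and flat priors:

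| No-difference scenario | Article | Simulated, SD 10.5 |
|---|---|---|
| Mean N | 4867 | 4876 |
| Percentiles 25/50/75 | 3950/4450/5450 | 3950/4450/5450 |
| Superiority | 0.9% | 1.1% |
| Equivalence | 99.1% | 98.9% |

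Across the 14 scenarios with differences (SD 10.55), mean N was 2238–4723 against 2265–4892 stated. The stated performance is therefore obtained without covariate adjustment, and no stated figure depends on the omitted variables.

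**Step 2: add explained variance.** The residual SD becomes 10.55 × √(1 − R²).

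| R² | Fall in SE, 1 − √(1 − R²) | Mean N, no difference | Saving | Mean N, one arm better by 1 day | Superiority in that scenario |
|---|---|---|---|---|---|
| 0 | – | 4914 | – | 4720 | 72.2% |
| 0.02 | 1.0% | 4833 | 81 | 4670 | 73.8% |
| 0.05 | 2.5% | 4722 | 192 | 4572 | 72.8% |
| 0.10 | 5.1% | 4554 | 360 | 4384 | 73.7% |

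The superiority column rests on 3000 runs per row, so its simulation error is √(0.73 × 0.27 / 3000) ≈ 0.8 percentage points. The column shows no material trend. The equivalence rule still ends about a quarter of those trials.

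**Step 3: sensitivity to the starting point.** The table starts from a model that explains nothing, whereas the current covariates explain an unknown share. Suppose that share is 10% (assumption), so the start is 4554. A further 2% of the residual gives a total R² of 1 − 0.90 × 0.98 = 0.118. A further 10% gives 1 − 0.90 × 0.90 = 0.19. Linear interpolation between the simulated values at 0.10 (4554), 0.15 (4376) and 0.20 (4133) gives about 4490 and 4182, savings of about 64 and 372. The order of magnitude is unchanged.

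**The case against.** The strongest reply is that nothing is wrong. The list is prespecified and coherent, covers both stratification variables and three organ-support markers, and cites a core protocol that is not at hand and may give the rationale. The stated operating characteristics reproduce without any covariates, and conclusiveness is already about 100% in every scenario. All of this stands, and it is why the point is an improvement and not a correction.

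A second reply is that no passage shows how well these variables predict days alive out of hospital beyond the current set. This also stands. It weighs most against lactate and systolic pressure, which may largely overlap with circulatory support. It weighs less against frailty and limitations of care, which measure things the current set does not. Body weight has no case as a precision covariate: that it sets the dose in one arm does not make it prognostic, and a main effect would not capture dose-by-weight effects.

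A third reply is that section 2.7.4 governs all outcomes, so more terms there would burden logistic models for rare safety events. That is right, and it is met by confining the change to the primary-outcome model.

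A reader might go further and infer that strong predictors are being discarded at no saving, or might scale 4867 directly by the variance reduction, which gives 97 at 2% and 487 at 10%. The documents do not support either. Prognostic strength is not reported, the omission does save imputation and model terms, and expected N in a design with discrete looks and a lag does not shrink in proportion: the simulated savings are 81 and 360.

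**Conclusion.** The point holds as an optional gain in efficiency. Two baseline variables that are already recorded, and that plausibly carry prognostic information the current set lacks, are left out of the primary-outcome model. If they explain 2–10% more of the residual variance, the standard error falls by about 1–5% and expected N under no difference falls by roughly 80–360, less than one 500-participant interval between analyses. The probability of declaring superiority at a 1-day difference stays at 72–74%, so the gain is earlier average stopping and narrower intervals, not better power.

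These sizes rest on the assumed R² range, an SD of about 10.5 days and a lag of 450 participants; the article states none of the three. Bias, an inflated type 1 error or a contradiction in the plan might be inferred from the omission, but none follows from it.

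**What to change.** Before the first adaptive analysis at 1500 participants, amend section 2.7.4 so that the linear model for days alive out of hospital at 30 days also adjusts for the Clinical Frailty Scale and for limitations of care (yes/no). State the functional form for frailty; the linear and quadratic terms already used for age would be consistent. Handle missing values with the multiple imputation planned in 2.7.6, and report the current covariate set as a sensitivity analysis. Leave the logistic models for sparse safety outcomes unchanged. Lactate and systolic pressure are optional. Do not add body weight for precision.

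The cost is a short amendment, some imputed covariate values, and extra terms to validate and fit at each of up to 18 adaptive analyses ((10,000 − 1500)/500 + 1). It also departs from the covariate set cited to the core protocol, in an open-label domain where screening has begun. The change should therefore be fixed and dated before any comparative result is seen.

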#### Heterogeneous Intervention Effects and Interactions

2.7.5

Once the domain is stopped, potential heterogeneous intervention effects for the primary outcome according to the baseline characteristics in Table 5 will be assessed on both the absolute and relative scales. For all analyses of heterogeneous intervention effects, results will be visualised with 95% credible intervals and interpreted probabilistically for all comparisons. No assessment of potential interactions with other domains is planned.

**TABLE 5 aas70199-tbl-0005:** Analyses of heterogeneity of intervention effects for the primary outcome.

Baseline characteristics	Definition and type	Expected direction of interaction
Disease severity	Baseline disease severity according to the Simplified Mortality Score for the Intensive Care Unit [39] (SMS‐ICU); continuous	Larger beneficial effects of the weight‐based dose compared to the other two doses in patients with more severe disease Similar effects of fixed low versus intermediate dose irrespective of severity
Risk of VTE	Baseline risk of VTE according to a modified version of the ‘Predicting the Risk of Venous Thromboembolism in Critically Ill Patients’ score [41] (PROVE‐IT); continuous	Larger beneficial effects of the weight‐based dose compared to the other two doses in patients with higher risk of VTE Similar effects of fixed low versus intermediate dose irrespective of VTE risk
Renal function	Highest plasma creatinine in the 24 h prior to randomisation; continuous	No substantial interactions between renal function and arms
Platelet count	Lowest platelet count in the 24 h prior to randomisation; continuous	No substantial interactions between platelet counts and arms

*Note:* Heterogeneity of intervention effects on the primary outcome will be analysed according to the baseline characteristics outlined in this table. The analyses of heterogeneity in intervention effects according to the continuous baseline variables listed above will be performed using linear regression models similar to the primary analysis model, but also including the baseline characteristic of interest, using linear and quadratic terms and their interactions with the intervention group (after mean‐centring and, for variables expected to be substantially right‐skewed, log 2‐transformation). Mean values for the primary outcome will be predicted in each intervention group across the full range of values of the baseline variable of interest using a G‐computation approach described in the full domain‐specific appendix [29] and used to calculate differences on the absolute and relative scales.

Abbreviations: PROVE‐IT, *Predicting the risk of venous thromboembolism in critically ill patients* [41]; SMS‐ICU, *Simplified Mortality Score for the Intensive Care Unit* [39]; VTE, venous thromboembolism.

#### Missing Data Handling

2.7.6

Proportions of missing data will be presented, and missingness handled using multiple imputation with best‐worst/worst‐best case sensitivity analyses according to the core protocol [28, 29, 42].

#### Statistical Simulation and Performance Metrics

2.7.7

The *INCEPT‐Thromboprophylaxis* domain design has been developed and evaluated using statistical simulation via R v4.5.0 (R Core Team, R Foundation for Statistical Computing, Vienna, Austria) with the *adaptr* R package (https://inceptdk.github.io/adaptr) following the approach previously described and used [35, 37, 43]. The final design as well as sensitivity analyses with different design choices and key assumptions were all evaluated using 100,000 simulations under multiple clinical scenarios. In brief, we assumed that the distribution of the primary and guiding outcome in the different doses of LMWH arms resembled the distribution from the *AFIB‐ICU* cohort study [44]. This reference distribution was modelled using a *binomial* distribution handling the probability of having 0 or > 0 days, and a *beta* distribution modelling the distribution among those with > 0 days. In summary, 43.6% had 0 days (22.3% due to death), with an estimated mean of 18 days in those with > 0 days, and an overall estimated mean of 10 days. Simulations were conducted in scenarios with no differences between arms, and with no, small and large differences in both directions between arms, corresponding to overall mean differences of 1 or 2 days in either direction. Performance metrics were assessed under a total of 15 realistic scenarios, constituting all unique combinations of the reference distribution in one arm and no/small/large differences in the other arms in both directions. Multiple performance metrics were evaluated, with the key metrics presented in Table 6. The expected sample sizes across scenarios ranged from 2265 to 4892 participants, with approximately 100% probabilities of conclusiveness across scenarios.

**TABLE 6 aas70199-tbl-0006:** Key performance metrics of the final domain design.

Metric	No differences	Ranges across scenarios with differences
Sample size—mean	4867	2265–4892
[25; 50; 75%‐percentiles]	[3950; 4450; 5450]	[1950–3450; 1950–4950; 2450–5950]
Mean number of days alive out of hospital at 30 days—mean	10.3 days	9.0–11.9 days
[25; 50; 75%‐percentiles]	[10.2; 10.3; 10.4]	[8.9–11.8; 9.0–11.9; 9.2–12.1]
Probability of conclusiveness	~100.0%	~100.0% to ~100.0%
Probability of superiority	0.9%	4.0%–99.9%
Probability of practical equivalence	99.1%	0.1%–96.0%
Probability of inconclusiveness	~0.0%	~0.0% to ~0.0%
Probability of erroneous superiority	0.1%	~0.0% to 4.6%
Root mean squared error (for estimated mean number of days in the superior arm, for simulations stopped for superiority only)	0.7 days	0.3–0.6 days
Ideal design percentage (for simulations stopped for superiority only)	—	100.0%–100.0%

*Note:* Key performance metrics of the final *INCEPT‐Thromboprophylaxis* domain design under the primary assumptions used based on 100,000 simulations for each scenario. The probabilities of conclusiveness correspond to the combined probabilities of superiority and practical equivalence; the probabilities of superiority may be interpreted as the type 1 error rate in the scenario with no difference and as the power in the scenarios with differences present. The probabilities of inconclusiveness refers to the proportion of simulated trials stopped at the maximum sample size without triggering any stopping rule. The probability of erroneous superiority refers to the probabilities of declaring one arm overall superior if it is not a single superior arm (i.e., if the arm is inferior to one or more other arms or if the arm is superior to one arm but equivalent to another arm). Ideal design percentages are calculated as described elsewhere; this measure cannot be calculated in the scenario where no differences between arms are present.

